### Health economic analysis

Health economic analysis will be carried out to compare the service use, costs and cost-effectiveness of cognitive behavioural therapy (CBT-UED) as adjunct to the TAU intervention in young people (aged 12–18 years) with UEDs.

Economic analyses will include a cost-effectiveness and a cost-utility analysis with the respective outcomes being; the cost per one unit change in the SDQ-E scores and the cost per QALY gained. Analyses will be carried out primarily on an intention-to-treat basis although other exploratory analyses, such as per-protocol, may also be considered. Data will be analysed at the end of the study; there are no planned interim analyses. Multiple regression methods will be applied to estimate mean differences in costs and effects, using baseline and follow-up data as the dependent variables and the group identifier as an independent variable. Data with missing observations due to loss to follow-up will be examined to determine both its extent and whether it is missing at random or is informative. If data are missing to a sufficient extent, the use of appropriate multiple imputation techniques will be considered.

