#### Economic outcomes

The main outcomes of interest will be unit changes in distress levels measured by the SDQ-E (the primary outcome of the RCT) [41, 42], and the QALY gain as measured with the EQ-5D-Y questionnaire at baseline (0 weeks) and 24-week time points. The EQ-5D-Y is a child version of the EQ-5D, which measures health-related quality of life (HRQoL) in young populations using an age-appropriate adjustment to the wording of the original questionnaire [52–54]. The EQ-5D-Y consists of five domains (mobility, self-care, usual activities (e.g. work, study, housework, family or leisure activities), pain/discomfort and anxiety/depression) and each is rated 1 (no problems), 2 (some problems), or 3 (a lot of problems) [54]. UK values will be applied to the distinct health states derived from the EQ-5D-Y to estimate the utility value for each participant at each time point, and the area-under-the-curve methods will be used to calculate the QALYs [53].

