#### Service use and costs

Economic analysis will be conducted from the perspective of the national health care system and personal and social services (NHS and PSS), but a wider perspective including costs borne by the participants and their families will also be considered. Potential costs will include lost education for children and lost time from work for parents. The costs of lost education will be estimated using a notional figure for the value of days in education. Intervention costs will include the time spent by CAMHS community therapists to deliver the intervention, including training and supervision costs. The Client Service Receipt Inventory (CSRI) will be adapted and administered to record participants’ use of health and social services for the 6-month periods before and after baseline, respectively [51]. The CSRI has been developed by members of King’s Health Economics and has been widely used in mental and physical health economic evaluations. The data collected through the CSRI will be used to calculate average service costs and total costs of care. All unit costs will be derived using routine data sources, such as the NHS reference costs [89] and the Unit Costs of Health and Social Care [90], as well as study-specific estimates where appropriate. Medication use, such as name/type of drug, dosage levels and frequencies, will be recorded and costs will be calculated based on prices from the *British National Formulary for Children* [91] and the Prescription Cost Analysis [92]. From these, a mean cost per intervention and a mean cost taking into account participant and carer costs will be estimated.

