### Statistical analysis

In accordance with Consolidated Standards of Reporting Trials (CONSORT) [94] principles, we will report all participant flow in the study. Descriptive statistics will be used to summarise assessments of feasibility and acceptability in terms of recruitment, dropout and completeness of therapy. The main efficacy analysis will be via intention-to-treat with data from all participants included in the analysis including those who do not complete therapy. When completion of the full battery of outcome measures is not possible, participants will be offered the opportunity to complete the primary outcome measure only, and as many of the main secondary outcome measures as are tolerated, in person, by telephone, or by email. Every effort will be made to follow up all participants in both arms for research assessments, and the analysis will use, where appropriate, statistical techniques for handling missing data, determined by the extent and distribution of missing data, and any identified demographic or baseline clinical predictors of missing data (age, gender, ethnicity, SDQ-E, UED severity, Severe/Other Mental Illness, borough). The primary hypothesis will be analysed using a linear mixed model allowing for the baseline measurement of SDQ-E and treatment assignment as fixed effects, with SDQ-E at 4 months as the dependent variable. Therapist effects will be modelled by including a random effect for each therapist in the therapy arm, with the control-arm participants considered as being in individual clusters of size 1. The use of a mixed (random)-effect models will allow for estimation of the intra-cluster correlation coefficient, a measure of the proportion of variance in outcome because of therapist effects, which can be used in future applications; no estimate of this is currently available. Secondary outcome measures (excluding economic outcomes) will be analysed using the same approach.

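### The economic regression puts baseline data on the outcome side and states no baseline adjustment, which costs precision and leaves the QALY difference most exposed to chance imbalance

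*Protocol article*

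**What the plan says.** The Health economic analysis section of the protocol article states: "Multiple regression methods will be applied to estimate mean differences in costs and effects", and then assigns the variables their roles: "using baseline and follow-up data as the dependent variables and the group identifier as an independent variable".

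The Economic outcomes section takes as effect measures the unit change in SDQ-E and "the QALY gain as measured with the EQ-5D-Y questionnaire at baseline (0 weeks) and 24-week time points". It adds that "the area-under-the-curve methods will be used to calculate the QALYs". The Service use and costs section records "use of health and social services for the 6-month periods before and after baseline, respectively", so a pre-randomisation cost will exist for each participant.

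The Statistical analysis section treats baseline differently. The model for the primary hypothesis is described as follows: "linear mixed model allowing for the baseline measurement of SDQ-E and treatment assignment as fixed effects, with SDQ-E at 4 months as the dependent variable". That approach is then extended to other outcomes with an exception: "Secondary outcome measures (excluding economic outcomes) will be analysed using the same approach".

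The sections on economic outcomes, service use, bootstrap analysis and sensitivity analysis do not name baseline utility, prior cost or baseline SDQ-E as a covariate.

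**The concern.** A variable named as dependent cannot at the same time be the covariate that adjusts the comparison. Read literally, the sentence gives a regression of baseline on arm, which can only describe chance imbalance after randomisation, and a regression of follow-up on arm with no baseline term stated. This is a role that the protocol assigns, so it is more than a detail left for an analysis plan, and it differs from how the same protocol treats baseline in its primary model. SDQ-E makes the contrast plain: it is adjusted for baseline in the clinical analysis, but no adjustment is stated when it is the effect measure for cost-effectiveness.

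QALYs are the most sensitive outcome. With an area under the curve from two utility points, baseline utility is one of the two components of the outcome. Cost-effectiveness is one of the trial's three research questions, and these differences feed the cost-effectiveness planes and acceptability curves.

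**Working it through.** **Inputs from the protocol.** 60 randomised and 45 followed up per arm (Sample size); utilities at 0 and 24 weeks only (Economic outcomes); service use for six months before and six months after baseline (Service use and costs). The economic sections state no precision figure to reproduce. The design figure that uses 45 per arm does reproduce: a two-sided t test at 0.05 gives 80.4% power at 0.6 SD (stated: 80%) and 90.7% at 0.7 SD (stated: 90%). It is not in dispute.

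**Assumptions, not in the protocol.** Baseline-to-follow-up correlation r = 0.3, 0.5 or 0.7; equal SDs at the two times; utility SD 0.25 where an absolute QALY figure is given. The SE ratios in step 4 do not depend on the SD.

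**Step 1: weight of baseline utility.** QALY = (24/52) × (u0 + u24)/2. The weight on u0 is 12/52 = 0.231, so a baseline difference x adds 0.231x directly.

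**Step 2: how large chance imbalance is.** The SE of the baseline difference is SD × √(2/n).
- 45 per arm: √(2/45) = 0.211 SD, 95% range ±0.41 SD. A difference of at least 0.2 SD in either direction has probability 34%.
- 60 per arm: √(2/60) = 0.183 SD, 95% range ±0.36 SD; probability 27%.
- With SD 0.25 and 45 per arm: 0.25 × 0.211 = 0.053 utility. The direct part is 0.231 × 0.053 = 0.012 QALY, 95% range ±0.024. This scales in proportion to the SD (about 0.049 × SD).

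**Step 3: effect of a given imbalance on QALYs.** With no treatment effect and a baseline utility difference d, the expected unadjusted QALY difference is (24/52) × d × (1 + r)/2. With baseline utility as a covariate it is 0. The table takes d = 0.05, which is 0.2 SD. A simulation with 45 per arm and 4,000 runs at each r agreed (0.0150, 0.0172 and 0.0196 unadjusted; 0.000 adjusted). For scale, a true utility gain of 0.05 at 24 weeks from a balanced baseline is worth (24/52) × 0.05/2 = 0.0115 QALY.

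**Step 4: precision.** For QALYs the variance is proportional to 2 + 2r unadjusted and to 1 − r² adjusted, so the SE ratio is √((1 − r²)/(2 + 2r)) = √((1 − r)/2). Follow-up cost covers a separate window from prior cost, so a baseline cost difference carries over only as the fraction r, and the SE ratio is √(1 − r²). The same formula holds for follow-up SDQ-E at a given r.

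| r | QALY difference from d = 0.05, unadjusted | Same, adjusted | SE ratio, QALY | SE ratio, cost |
|---|---|---|---|---|
| 0.3 | 0.0150 | 0 | 0.59 | 0.95 |
| 0.5 | 0.0173 | 0 | 0.50 | 0.87 |
| 0.7 | 0.0196 | 0 | 0.39 | 0.71 |

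Of each unadjusted QALY difference, 0.231 × 0.05 = 0.0115 is baseline utility entering directly. The rest comes through the correlation.

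**The case against.** The sentence need not mean an unadjusted analysis. It speaks of multiple regression and calls the group identifier one independent variable, which leaves room for others. Naming baseline and follow-up together as outcomes could also point to change scores, since the Economic outcomes section speaks of unit changes and QALY gain, or to a joint repeated-measures model. A drafting slip is possible too. All of this stands as far as intent goes: a reader might infer that the trial will make no baseline adjustment, but the text supports only that none is stated.

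The alternatives do not repair the sentence. If QALY gain meant subtracting baseline utility held over 24 weeks, the outcome would be (24/52) × (u24 − u0)/2. An imbalance d would then carry over as −(24/52) × d × (1 − r)/2: for d = 0.05, −0.0081, −0.0058 and −0.0035 at r = 0.3, 0.5 and 0.7. That is smaller and of opposite sign, but not zero. A longitudinal model can properly hold baseline as an outcome if the arms are constrained to equal baseline means, but no such model or constraint is described.

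It is also fair that these are secondary analyses, that the primary analysis adjusts for baseline, and that a bootstrap which resamples participants would carry the variation from chance imbalance into the plane and the acceptability curve. The uncertainty would be wider, not hidden. The utility SD and the 0.05 imbalance are single assumed values, so the absolute QALY figures are illustrations.

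**Conclusion.** The point holds as a wrongly assigned role in the economic model, and it should be corrected. Baseline is placed on the dependent side, arm is the only regressor named, and no baseline adjustment is stated for costs, QALYs or SDQ-E.

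Two stronger readings are tempting and are not supported. One is that the economic results would be biased: under randomisation the unadjusted differences are unbiased over repetitions, so the harm is error conditional on the imbalance that occurs in this trial, and lost precision. The other is that baseline imbalance passes straight into every economic outcome: direct entry, at 0.23 per unit of utility, is true of QALYs only, while costs and SDQ-E are touched only through their correlation with baseline.

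The avoidable loss is substantial for QALYs and small to moderate for costs, across the assumed correlations of 0.3 to 0.7 with equal SDs. The primary clinical result is unaffected.

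**What to change.** Reword the regression sentence in the Health economic analysis section so that follow-up cost, QALY and follow-up SDQ-E are the dependent variables. The independent variables should be arm and the matching baseline value: cost over the prior six months, baseline EQ-5D-Y utility and baseline SDQ-E respectively. State in the Bootstrap analysis section that this adjusted regression is refitted in each bootstrap sample, so that the planes and acceptability curves rest on the adjusted differences. Adding the stratification factors is optional. If a constrained longitudinal model was intended, it should be described as such.

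The cost is one reworded sentence and one added clause. All the baseline data are already scheduled for collection. Making the change before the economic data are analysed also removes a later choice between adjusted and unadjusted results.

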#### Bootstrap analysis

To account for the likely skewed distribution of cost data, the non-parametric bootstrap method will be used to make cost comparisons between the two groups [95]. Bootstrapping involves repeatedly estimating the incremental cost-effectiveness ratio to account for the uncertainty surrounding the estimates of costs and effects. Likewise, using the net benefit approach, estimates of the proportion of iterations in which the intervention of interest has the maximum expected net benefit (NB), or equivalently, a positive incremental NB will be determined for a range of willingness-to-pay thresholds. The estimates will be produced by repeatedly sampling with replacement from the existing trial population [96]. The results of the bootstrap analyses will be plotted on cost-effectiveness planes (CEPs) and will be used to estimate cost-effectiveness acceptability curves (CEACs), which show the probability of the intervention to be cost-effective subject to a range of thresholds that society would be willing to pay for a unit improvement in the health outcome (e.g. QALYs) [97]. However, using change in distress levels (SDQ scores) as a measure of health status makes a meaningful interpretation of the CEACs difficult, as acceptance thresholds do not apply. In this case, thresholds at which the intervention has, e.g. above 60% likelihood of being cost-effective, will be explored.

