### Sample size

We will recruit 120 participants, randomly allocating 60 per group. From previous experience, we will allow for a conservative loss-to-follow-up of approximately 33% (85% follow-up achieved in an earlier pilot study [34]. With 45 successfully followed up in each group, we would have 80% power to detect between group differences for the smallest achieved effect sizes from previous studies of cognitive therapy with young people (0.6 SD) using a two-group *t* test with a 0.05 two-sided significance level. We will have 90% power to detect effect sizes of 0.7 SD and above. Our pilot work shows between group effect sizes of 0.6 in inpatients [32]. In practice, the power will be increased by using a mixed (random)-effects model allowing for baseline covariates including distress (rather than a simple *t* test) to gain precision in the effect estimates, but this increase is likely to be counteracted by allowing for modest between-therapist variation.

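### As written, the economic regressions and bootstrap have no therapist term, although the clinical analysis models therapist and SDQ-E is analysed in both; if therapists differ, economic uncertainty is modestly understated

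*Protocol article*

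**What the plan says.** The Statistical analysis section sets out a partially nested model for SDQ-E: "Therapist effects will be modelled by including a random effect for each therapist in the therapy arm", with each control participant treated as a cluster of one. It extends this to the other clinical outcomes but not to the economic ones: "Secondary outcome measures (excluding economic outcomes) will be analysed using the same approach". On the size of the therapist effect it says that "no estimate of this is currently available". The Sample size section expects the precision gained from baseline covariates to be offset: "this increase is likely to be counteracted by allowing for modest between-therapist variation".

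The Health economic analysis section says: "Multiple regression methods will be applied to estimate mean differences in costs and effects". The only explanatory variable that it names is treatment group: "using baseline and follow-up data as the dependent variables and the group identifier as an independent variable". Its two results are "the cost per one unit change in the SDQ-E scores and the cost per QALY gained". The Bootstrap analysis section describes the resampling: "The estimates will be produced by repeatedly sampling with replacement from the existing trial population". The Sensitivity analysis section varies only the intervention, lost-work and lost-education costs, and does so deterministically. None of these economic sections mentions therapist.

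**The concern.** SDQ-E is both the primary clinical outcome and one of the two economic effect measures. Followed literally, the plan compares the arms on this scale with therapist clustering in the clinical analysis and without it in the economic analysis, and it gives no reason for the difference. The trial could then report two different precisions for the effect on one scale.

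Young people treated by the same therapist may have correlated outcomes. Regression on the group identifier alone, or resampling participants one by one, treats them as independent. With a positive correlation, this understates the variance of the CBT-UED mean and hence of the difference between arms. The plan conveys cost-effectiveness uncertainty through bootstrap planes and acceptability curves. Cost-effectiveness is one of three research questions under Study aims, and the Discussion says the economic evidence may inform commissioning and policy.

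**Working it through.** **Inputs from the article.** 60 randomised and 45 analysed per arm; two-sided 5% test; 80% power at 0.6 SD and 90% at 0.7 SD (Sample size). Two to four trial cases per therapist and a peak combined caseload of 24 (Therapists).

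**Inputs not in the article (assumptions).** ICC of 0.01, 0.02, 0.05 or 0.10. Total number of therapists of 6, 8, 12 or 24. The caseload figures imply 24/4 = 6 to 24/2 = 12 therapists at full load. That is a concurrent number, and therapist input is staggered, so 24 is included as a larger total.

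**Step 1: the plan's own figure.** A two-sample t test with 45 per arm gives 80.4% power at 0.6 SD and 90.7% at 0.7 SD. Both stated figures reproduce. (45 of 60 is a 25% loss, although the text says about 33%. I use 45 because the power statement does.)

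**Step 2: effect of ignoring clustering in one arm.** With m = 45/(number of therapists), the design effect in the CBT-UED arm is DE = 1 + (m − 1) × ICC. In the TAU arm it is 1. With equal total variance in both arms, the correct standard error divided by the unclustered one is r = √((DE + 1)/2).

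Example with 6 therapists and ICC 0.10: m = 7.5, DE = 1 + 6.5 × 0.10 = 1.65, r = √(2.65/2) = 1.151.

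| Therapists | m | ICC 0.01 | ICC 0.02 | ICC 0.05 | ICC 0.10 |
|---|---|---|---|---|---|
| 6 | 7.50 | 1.016 | 1.032 | 1.078 | 1.151 |
| 8 | 5.63 | 1.011 | 1.023 | 1.056 | 1.110 |
| 12 | 3.75 | 1.007 | 1.014 | 1.034 | 1.067 |
| 24 | 1.88 | 1.002 | 1.004 | 1.011 | 1.022 |

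The unclustered standard error is too small by 1 − 1/r. That is 0.2% at r = 1.002 and 13% at r = 1.151. At ICC 0, r = 1. With 40 analysed per arm instead of 45, the largest ratio falls to √((1 + 5.67 × 0.10 + 1)/2) = 1.13.

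**Step 3: coverage.** On a normal approximation, a nominal 95% interval covers 2Φ(1.96/r) − 1. This is about 95% at r = 1.002 and 91.1% at r = 1.151.

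**Step 4: acceptability curve.** A probability Φ(z) from the unclustered analysis becomes Φ(z/r). At the worst case in the table, 0.90 becomes Φ(1.2816/1.151) = 0.867 and 0.60 becomes 0.587.

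**Step 5: simulated individual-level bootstrap** (3,000 trials, 400 resamples each, percentile intervals, normal outcomes).

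| Therapists, ICC | True SE / mean bootstrap SE | Coverage |
|---|---|---|
| No clustering | not computed | 93.4% |
| 12, 0.02 | 1.03 | 93.2% |
| 12, 0.05 | 1.08 | 92.7% |
| 6, 0.05 | 1.09 | 92.0% |
| 6, 0.10 | 1.15 | 90.3% |

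The Monte Carlo error on coverage is about √(0.93 × 0.07/3000), or 0.5 points. The fair comparator is 93.4%, not 95%, because the percentile bootstrap already under-covers slightly at this sample size. Clustering therefore accounts for a loss of about 0 to 3 points in these runs.

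**The case against.** The strongest reply is that silence is not a decision. The exemption of economic outcomes may only point the reader to the separate economic section. The text does not specify ordinary least squares, and the bootstrap sentence is a generic description that names no resampling unit. A fuller economic plan, not shown, may specify clustering. So a reader might infer that the authors chose to ignore therapist effects, and the article does not support that. What stands is narrower: the exemption is explicit, the article names the methods that apply instead, and nothing in the economic sections brings therapist back.

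A reader might also infer that the economic intervals are certainly too narrow. That is not supported either. No ICC is given, the expectation of modest variation concerns the power of the distress analysis, and at an ICC of 0.01 to 0.02 the ratio is at most 1.032.

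A third tempting reading is that costs are at least as clustered as outcomes, because therapist time, training and supervision enter the intervention cost. The Service use and costs section does not say that training is charged therapist by therapist. If it is spread as an average, it adds a constant and no between-therapist variance.

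The practical effect is also small. The clinical inference is untouched, the article itself says SDQ-E acceptability curves are hard to interpret, and it calls for replication. This limits the weight of the point but does not remove the inconsistency.

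**Conclusion.** The point holds in a conditional form. The clinical analysis allows for therapist, the economic methods as written do not, and one scale passes through both. The direction of error is known if therapists differ. Its size is small to moderate: under the assumed ICC and therapist numbers, the unclustered standard error is 0% to 13% too small. Only combinations of few therapists and an ICC of 0.05 or more make a visible difference. For costs and QALYs the article gives no information on therapist variation, so the same range applies there purely by assumption. This is worth correcting because it is cheap and the economic question is a named aim. It does not threaten the trial's main conclusion.

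**What to change.** In Health economic analysis and Bootstrap analysis, apply the partially nested structure of the Statistical analysis section to costs, QALYs, SDQ-E and net benefit: therapist clusters in the CBT-UED arm, TAU participants as singletons. Derive the acceptability curves from that model. Alternatively, resample separately within arm, in a way that respects therapist in the CBT-UED arm (therapists, then participants within therapist) and by individual in the TAU arm. Because there may be few therapists, either could be specified at least as a sensitivity analysis beside the unclustered result. If clustering is to be left out, state that and give the reason.

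Therapist identity is already needed for the clinical model, so no new data are required. The cost is a short change of wording, a little programming, slightly wider intervals and slightly flatter acceptability curves.
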